### Recruitment and consent to participate

Eligible patients will be offered the opportunity to participate in the study by their radiologist or their surgeon. Patients who agree to participate in this study will provide oral consent for enrolment and the investigator will sign a document demonstrating that the patient has been informed and has agreed to participate. Data obtained will be retained with consent, and any reasons given for withdrawal will be recorded. Participants can withdraw at any time.

### Sample size calculation

The satisfaction score is a continuous score taking values between 0 and 10 points. To be able to show a minimum effect size of ¾, corresponding to a difference of about 23% of the overall score, for an estimated standard deviation of about 1.5 points, with a power of 80%, and considering a type I error rate of 5%, a number of 30 patients per group would be necessary. To take into account a rate of non-matchable patients of about 20%, as well as a rate of non-evaluable patients of about 10%, 40 patients will be included in each group, for a total of 80. Given the lack of preliminary data, and the uncertainty around the assumptions used for sample size calculation, an interim analysis will be performed after approximately half of the initially planned number of subjects has been included. The purpose of the interim analysis is to re-estimate the number of subjects needed based on the distribution of scores, in order to ensure sufficient statistical power of the study. Since no early ending is planned after the interim analysis, the alpha risk will not be adjusted, and the formal comparison between the two groups by hypothesis testing will be done only at the final analysis.

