### Statistical analysis

#### Primary analysis

The main analysis consists of comparing the patient satisfaction scores between the two groups, RFID vs. gold standard, and, if the difference in mean scores is clinically significant (difference of about 20%), to test whether it is statistically significant using Student’s t-test or a non-parametric test depending on the nature of the data. A propensity score matching will be performed beforehand to compensate for the non-randomized design of the study. We will include in the calculation of the propensity score the anxiety measured by the HAD scale at inclusion, the only measurable confounding factor we estimate being related to the primary outcome.

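### The percentage in the sample size calculation does not match its effect size and SD on the 0-10 scale (1.125 points is 11%, not 23%), and the 20% condition on the primary test shares the unstated base

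*Protocol article*

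**What the plan says.** All of this is in the protocol article.

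- **Sample size calculation, the scale:** "The satisfaction score is a continuous score taking values between 0 and 10 points".
- **Sample size calculation, the inputs:** the next sentence gives three linked figures: "minimum effect size of ¾, corresponding to a difference of about 23% of the overall score, for an estimated standard deviation of about 1.5 points". At 80% power and a 5% type I error rate these lead to 30 patients per group, raised to 40 per group (80 in total) for non-matchable and non-evaluable patients.
- **Sample size calculation, the interim analysis:** the number of subjects is to be re-estimated from the distribution of the scores after about half of the planned inclusions.
- **Primary analysis:** the hypothesis test is carried out "if the difference in mean scores is clinically significant (difference of about 20" per cent). The base of that percentage is not given.

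No expected mean score is stated for either group.

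**The concern.** Effect size, SD and raw difference are tied together: any two fix the third. Here the effect size and the SD give one difference, and the percentage, read on the scale defined in the sentence before, gives another about twice as large.

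Two parts of the plan need a difference in points. The interim re-estimation cannot turn an observed SD into a sample size without one. The condition on the primary test needs a threshold in points before anyone can say whether an observed difference meets it. If the base of the percentages is unclear, both can be applied in very different ways to the same data.

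**Working it through.** **Inputs.** From Sample size calculation: scale 0-10, effect size d = 0.75, SD 1.5, difference about 23%, power 80%, alpha 5%, 30 per group. From Primary analysis: threshold about 20%. The sidedness of the 5% is not stated there; two-sided is assumed.

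**1. The plan's own figure.** Normal approximation: n = 2(1.96 + 0.84)²/d² = 15.7/0.5625 = 27.9, so 28 per group. The exact t-test gives 28.9, so 29. Dividing the t-test figure by the Wilcoxon efficiency of 0.955 gives 30.3. The stated 30 is reproduced, with t-test power of 81.5%. A one-sided 5% level gives only 22 to 23, which supports the two-sided assumption.

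**2. The difference implied by d and SD.** 0.75 × 1.5 = 1.125 points; 1.125/10 = 11.25% of the scale.

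**3. The difference implied by 23% of the scale.** 0.23 × 10 = 2.3 points. The ratio to step 2 is 2.3/1.125 = 2.04.
- Keeping SD 1.5: d = 2.3/1.5 = 1.53, which needs 7 (normal) or 8 (t-test) per group, not 30.
- Keeping d = 0.75: SD = 2.3/0.75 = 3.07, not 1.5.

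**4. The base that would reconcile all the figures.** 1.125/0.23 = 4.89. With a mean of 5, 1.125/5 = 22.5%.

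**5. The condition on the primary test.** With SD 1.5 and 30 per group, the standard error of the difference is 1.5 × √(2/30) = 0.387. For a true difference of 1.125 points:

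| Meaning of 20% | Threshold | z | Chance that the observed difference reaches it |
|---|---|---|---|
| of the 0-10 scale | 2 points | (2 − 1.125)/0.387 = 2.26 | about 1% |
| of a mean of 5 | 1 point | (1 − 1.125)/0.387 = −0.32 | about 63% |

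Significance at the two-sided 5% level needs an observed difference of only about 1.96 × 0.387 = 0.76 points. On either meaning the threshold, not the p-value, is therefore the harder hurdle.

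For comparison, take the other consistent set: true difference 2.3 points, SD 3.07, threshold 2 points. The standard error is 3.07 × √(2/30) = 0.79, z = (2 − 2.3)/0.79 = −0.38, and the chance is about 65%. The 1% figure thus arises when the printed effect size and SD are combined with a threshold read as a share of the scale.

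**6. The re-estimation.** For any observed SD, the required n is proportional to 1/difference². The ratio between the two targets is (2.3/1.125)² = 4.18 in the normal approximation. By t-test at SD 1.5 the two targets need 29 and 8 per group. At an assumed SD of 2 they need 51 and 13, one above and one below the planned 30 evaluable patients per group.

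**The case against.** The best defence is that only the percentage is loosely worded. The effect size and the SD in points are both printed, and together they fix 1.125 points, so the planned difference is recoverable. Read as a share of an expected mean near the midpoint of the scale, 23% is right to rounding. On the same base the 20% threshold becomes 1.0 point, just under the planned 1.125. Every printed figure is then true. This is plausible, but it remains an inference: no mean is stated, and the percentage is attached to the overall score directly after that score has been defined as 0 to 10.

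Three stronger readings are tempting, and the document does not support them.

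- **That the sample size of 80 is undermined.** It is not. The 30 per group before inflation rests only on d = 0.75, power and alpha, and it reproduces. Either consistent set of inputs leaves it unchanged.
- **That the trial is badly underpowered.** A reader might pair the 1.125-point difference with an SD near 3. That takes the difference from one reading and the SD from the other; each consistent set has d = 0.75. Nor is there a power deficit in the t-test if the relevant difference is 2 points at SD 1.5: that effect size, 2/1.5 = 1.33, needs only about 10 per group.
- **That 23% is put forward as the clinically relevant difference.** The article does not say so. Only the 20% in Primary analysis is called clinically significant.

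It is also fair to say that the article does not state which target the re-estimation will use, and the full protocol may. The fourfold gap is what follows if the choice is left open, not a forecast of what will be done.

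**Conclusion.** The point holds as an inconsistency in the stated inputs. On the 0-10 scale, d = 0.75 with SD 1.5 is 1.125 points, or 11%; the printed 23% is about twice that and is right only against an unstated mean of about 5. The stated 30 per group is sound.

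The practical weight lies in the condition on the primary test, whose 20% also lacks a base. If it means 2 points, a true difference equal to the one implied by the printed effect size and SD would almost never reach the test (about 1%). If it means 1 point, it would do so about 63% of the time. These figures assume a normal sampling distribution, SD 1.5, 30 evaluable patients per group, and no effect of matching on the variance. Even the favourable reading is below the nominal 80%, because the threshold lies close to the planned difference. The fourfold spread in a re-estimated sample size is the second consequence.

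**What to change.** In Sample size calculation, state the target difference in points with an SD and an effect size that match it, and name the base of any percentage. Two consistent forms are available, and only the authors know which was meant:

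- 1.125 points, SD 1.5, d = 0.75, described as 11% of the scale, or as about 23% of an expected mean near 5 if that mean is stated; or
- about 2.3 points (23% of the scale), SD about 3, d = 0.75.

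Name that difference in points as the target of the interim re-estimation. The interim falls after about half of the 80 inclusions, and Trial status reports 64 patients recruited. If the re-estimation has already been done, report the target that was used.

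In Primary analysis, express the 20% threshold in points on the same base, so that it agrees with the planned difference.

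The cost is wording only. The 30 per group and the total of 80 do not change under either form.

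### At the stated loss rates, 40 patients per group leave about 28 to 29 for analysis, not the 30 called necessary; the effect on power is minor

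*Protocol article*

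**What the plan says.** The section on sample size calculation in the protocol article gives every input to the enrolment figure. The target is "To be able to show a minimum effect size of ¾", "for an estimated standard deviation of about 1.5 points", "with a power of 80" per cent and "considering a type I error rate of 5" per cent. From these it concludes that "a number of 30 patients per group would be necessary". It then allows for "a rate of non-matchable patients of about 20%, as well as a rate of non-evaluable patients of about 10" per cent, and sets the enrolment: "40 patients will be included in each group, for a total of 80".

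The section does not say how the two loss rates are combined or whether the same patient may count under both. It plans an interim re-estimation of the sample size, driven by the observed distribution of scores, because the assumptions are uncertain. The primary analysis section compares the groups after propensity score matching, with a t-test or a non-parametric test.

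**The concern.** An allowance for losses should bring the expected number left after the losses back to the number required. Here the required number, the two loss rates and the enrolled number all stand in the same paragraph, and they do not fit. An enrolment of 40 that must leave 30 implies a combined loss of 25%. Rates of 20% and 10% give 28% if they act independently and 30% if they fall on different patients.

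At stake is whether the stated enrolment delivers the analysable number to which the protocol ties its power, and whether a reader can rely on the same inflation if the number of subjects is revised.

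**Working it through.** **Inputs, all from the sample size section:** standardised effect 0.75; power 80%; type I error 5%; 30 required per group; about 20% non-matchable; about 10% non-evaluable; 40 enrolled per group. Sidedness is not stated for the primary test. I assume two-sided, because a one-sided test needs only 22 to 23 per group and does not fit the stated 30.

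**Step 1. Reproduce the 30.**
- Normal approximation: n = 2 x (1.960 + 0.842)² / 0.75² = 2 x 7.85 / 0.5625 = 27.9, so 28 per group.
- Exact two-sample t-test: 28.9, so 29 per group.
- Non-parametric test, with efficiency 0.955 relative to the t-test (an assumption that holds for near-normal scores): 28.9 / 0.955 = 30.3.

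The stated 30 is therefore reproduced within 2 patients. It carries about one patient of margin for the t-test and none for the non-parametric test.

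**Step 2. Apply the stated losses to 40.**
- One after the other: 40 x 0.8 x 0.9 = 40 x 0.72 = 28.8.
- Added: 40 x (1 - 0.30) = 28.0.

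**Step 3. Enrolment that would keep 30.**
- One after the other: 30 / 0.72 = 41.7, so 42 per group (84 in total).
- Added: 30 / 0.70 = 42.9, so 43 per group (86 in total).

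**Step 4. Where 40 may come from.** 30 x 1.2 x 1.1 = 39.6, which rounds to 40. That is multiplying up by the loss rates instead of dividing by the retained fraction. The protocol does not give its method, so this is an inference.

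**Step 5. Power at effect size 0.75, two-sided 5%.**

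| Analysable per group | t-test | Non-parametric (efficiency 0.955) |
|---|---|---|
| 28 (losses add) | 78.7% | 76.8% |
| 28.8 (one after the other) | 79.9% | 78.0% |
| 29 | 80.1% | 78.2% |
| 30 (stated as necessary) | 81.5% | 79.7% |

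The shortfall against 30 is 1 to 2 patients per group. Against the 80% target it costs 0.1 to 1.3 percentage points with the t-test.

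**The case against.** Four points can be made for the plan.

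- **The rates are approximate.** With 18% and 9%, 40 x 0.82 x 0.91 = 29.8 remain; with 17% and 10%, 40 x 0.83 x 0.90 = 29.9. This stands as a reason not to make much of the gap. It does not make 40 follow from the rates as written.
- **The losses may overlap.** If some patients are both non-matchable and non-evaluable, the combined loss can be anywhere from 20% upwards, and 25% is possible. That would need an overlap of 20 + 10 - 25 = 5 percentage points, so half of the non-evaluable patients would also be non-matchable. Independence gives 0.2 x 0.1 = 2 points. The text claims no such overlap.
- **The 30 is already rounded up.** The t-test needs 28.9, and from the normal-approximation figure of 28 the additive allowance gives 28 / 0.70 = 40 exactly. This stands, and it is why power barely moves. But the plan names 30, not 28, as the necessary number.
- **The interim re-estimation can revise the number.** It can, but it is described as resting on the distribution of scores, and nothing says that it would revisit the loss allowance.

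A reader might also infer stronger things. One is that each non-evaluable patient removes a matched partner, so that the loss is larger. The documents give no basis for this: matching comes before the group comparison, formal testing is done only at the final analysis, and no rule for dropping pairs is stated. Another is that the interim re-estimation repeats the slip. The article does not say that the same allowance is reused, and that step has probably passed: the patient selection section places it with the first 20 patients per group, and the trial status section reports 64 recruited.

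**Conclusion.** The enrolment figure does not follow from the stated inputs. Forty per group leaves about 29 patients if the losses apply one after the other and 28 if they add, where the protocol says 30 are necessary. This holds unless the two losses overlap substantially.

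The point is minor. Power stays at 78.7% to 79.9% with the t-test, and falls to about 77% to 78% only with the non-parametric option. It would be wrong to conclude that the trial is materially underpowered for this reason: the t-test needs 28.9 per group, so the slip mainly uses up the rounding margin in the 30. These figures assume a two-sided 5% test, an effect size of 0.75, the loss rates at their stated values and, for the non-parametric test, an efficiency of 0.955.

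**What to change.** Keep 80 patients and correct the statement:

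1. Say how the two rates combine: one after the other (retained fraction 0.72) or added (0.70).
2. Restate that 40 per group is expected to leave about 28 to 29 analysable patients per group, with about 79% to 80% power at effect size 0.75 under the t-test, or about 77% to 78% if a non-parametric test is used. Once the combination rule is chosen, give the single figure that goes with it.
3. In any further re-estimation of the number of subjects, divide the required analysable number by the retained fraction (0.72, or the fraction observed so far) instead of multiplying up by the loss rates. Use the same fraction here as in items 1 and 2.

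The cost is a sentence or two in the sample size section and, if the number is re-estimated again, one divisor. No patients are added and the design does not change; the stated power becomes slightly less favourable. A sponsor who wants to hold to 30 would need 42 or 43 per group, but a gap of this size does not call for that.

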### Patient selection

Inclusion and exclusion criteria are presented in Table 2. Patients over 18 year’s old requiring conservative surgery for an histologically proven non-palpable breast lesion (fibroadenomas, papillomas, atypical lesions and neoplasia) will be included.

**Table 2 Tab2:** Inclusion and non-inclusion criteria

**Inclusion criteria**	• Female over 18 years old • Requiring conservative surgery for an histologically proven non-palpable breast lesion (fibroadenomas, papillomas, atypical lesions and neoplasia) • Speaking and understanding French • Patients referred to senology for localization of non-palpable breast lesions by surgeons • Affiliated to the French Social Security System • Able to give informed consent
**Non-inclusion criteria**	• Multiple breast lesions • Patients with breast neoplasia during pregnancy • Persons deprived of liberty or under guardianship or incapable of giving consent • Refusal to participate

The estimated duration of patients’ enrolment is 1 year and 6 months: 80 patients will be enrolled and followed from the inclusion until one month after surgery. A sequential inclusion in time will be performed: 20 inclusions in the control group (gold-standard) during 3 months, then 20 patients in the “RFID group” for the following 3 months with an interim statistical analysis, before repeating the inclusion scheme. When patients consent to participate in the study, they are informed of the device they will receive. Patients of the hookwire group are convened the day before the surgery to install the device. Patients with the RFID tag have the device installation at least one week before their surgery.

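### Leaving alpha unadjusted because there is no early stopping is not a valid reason; what matters is whether the interim re-sizing uses the observed group difference, which the text leaves open

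*Protocol article*

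**What the plan says.** Under Sample size calculation, the protocol article plans an interim analysis at about half of the planned enrolment. The reason given is a lack of preliminary data and uncertainty about the planning assumptions. Its purpose is to "re-estimate the number of subjects needed based on the distribution of scores", so that power is sufficient. The article then says: "Since no early ending is planned after the interim analysis, the alpha risk will not be adjusted". It adds that the groups are formally compared only at the final analysis.

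The planning assumptions are stated in the same paragraph: "To be able to show a minimum effect size of ¾", "for an estimated standard deviation of about 1.5 points", 80% power, 5% type I error, and "a number of 30 patients per group would be necessary", raised to 40 per group for losses.

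Under Patient selection, enrolment runs as 20 hook-wire patients, "then 20 patients in the “RFID group” for the following 3 months with an interim statistical analysis", after which the scheme repeats. Patients are told at consent which device they will receive.

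Under Primary analysis, a Student or non-parametric test follows propensity-score matching, and only if the mean difference is about 20%.

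**The concern.** The sentence on alpha gives a reason, and the reason is wrong. Early stopping is one route to inflation. Changing the sample size in response to the observed difference is another, and it works with no stopping and no interim test. A large interim difference keeps the trial small, so the early data keep a large share of the final estimate. A small one brings in many new patients and dilutes the early data. The ordinary final t-test takes no account of this dependence.

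Alpha is safe if only the SD is updated, the target difference stays fixed and the size cannot fall. The wording does not limit the re-estimation in that way. Scores in general are named as its basis, the assumptions called uncertain include an effect size as well as an SD, and at the interim one full block of each device is complete with the device known. At stake is whether the 5% attached to the primary test is the error rate it actually has.

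**Working it through.** **1. The plan's own figure.** Inputs, from Sample size calculation: effect size 0.75, SD 1.5, power 80%, alpha 5% (sidedness not stated).

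- Normal formula, two-sided: n = 2(1.960 + 0.842)² / 0.75² = 27.9, so 28 per group. The exact t-test gives 28.9, so 29. Dividing by 0.955 for a rank test gives 30.3.
- One-sided, the same formulas give 22 to 23, so the stated 30 is a two-sided calculation.
- Losses of 20% and 10%: 30 / (0.8 × 0.9) = 41.7, or 30 × 1.3 = 39. The stated 40 lies between.

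The stated size reproduces.

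**2. What the re-estimation could mean.** With s the interim SD, the re-sized number per group is N = 2(1.960 + 0.842)² s² / d². The two readings differ in d:

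- SD-only: d is fixed at 0.75 × 1.5 = 1.125 points, the difference that reproduces the plan.
- Effect-based: d is the difference observed between the two devices at the interim.

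**3. Type I error of the unadjusted final t-test.** Null trials with normal scores, SD 1.5, 400,000 runs per scenario (Monte Carlo standard error √(0.05 × 0.95 / 400,000) = 0.03 percentage points). The interim is at half of the plan, N may rise but not fall below plan, and the final test is a two-sided 5% t-test on all data. The rule and the cap on N are assumptions, because the article gives neither.

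| Re-sizing rule | 20 of 40 per group, cap 2× / 4× | 15 of 30 per group, cap 2× / 4× |
|---|---|---|
| None | 5.0% / 5.0% | 5.0% / 5.0% |
| SD of all scores, device ignored; difference fixed | 5.0% / 5.0% | 5.0% / 5.0% |
| Within-group SD; difference fixed | 5.0% / 5.0% | 5.1% / 5.1% |
| Observed difference, either direction | 6.0% / 6.7% | 6.0% / 6.6% |
| Observed difference, only when it favours RFID | 5.5% / 5.8% | 5.5% / 5.8% |
| Raise N only if conditional power is 30–80% | 4.7% / 4.6% | 4.7% / 4.6% |
| Most unfavourable choice of N after seeing the difference | 6.2% / 6.8% | 6.2% / 6.9% |

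No scenario stops early or tests at the interim, yet the error rate runs from 4.6% to 6.9%. What is re-estimated, and by which rule, accounts for the spread.

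**4. The two-step rule in Primary analysis.** The test is run only if the mean difference is about 20%. Read as 2 points on the 0–10 scale at SD 1.5, the condition and test together reject in under 0.1% of null trials in every scenario above. With a 1-point condition they reject in 0.2% to 1.0% of them.

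**5. The fixed difference is not settled in the document.** 0.75 × 1.5 = 1.125 points, and 1.125 / 10 = 11% of a 0–10 score. Sample size calculation equates the effect size with about 23% of the score, and Primary analysis uses about 20%. An SD-only rule needs one of these in points.

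**The case against.** The strongest reply is that the article nowhere says the re-estimation is done by group or on the observed difference. It calls the effect a minimum, which is naturally a fixed target, calls the SD estimated, and rules out an interim hypothesis test. An SD-only reading is at least as natural, and under it alpha is 5.0%. The operating details may also stand in the approved full protocol, which is not shown. This stands as far as it goes: the document does not establish that re-sizing uses the group difference, and the missing floor or cap is not in itself the fault. What remains is a stated justification that would not be sound even if the procedure behind it were.

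The second reply is the condition of about 20%. At the planning SD it keeps the two-step false-positive rate below 5%, so a reader should not infer that the primary superiority claim as a whole exceeds 5%. This stands too. However, the article does not offer that condition as its reason for leaving alpha alone, and it does not define the 20% in points.

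Three stronger inferences are tempting and are not supported:

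- **Errors of 7% or more.** Effect-based re-sizing reaches 7.0–7.7%, and the most unfavourable choice 8.9–9.6%, only if N may also fall, down to or almost to the interim size. That fits poorly with a plan that excludes early ending and aims to secure power.
- **Group means shown to staff, leading to selective enrolment.** The article does not say that any interim result is released. Known consecutive blocks carry that risk with or without an interim.
- **N was in fact changed on the difference.** The article reports 64 recruited, past the interim point of about 40. It still gives 80 as the total and expects to finish 18 months after the May 2021 start, as planned. That suggests no change, though it does not prove it.

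**Conclusion.** The point holds in a limited form. The reason given for not adjusting alpha is invalid, and the wording leaves open both a procedure that keeps 5.0% and one that does not. If N is re-set on the observed difference and may only rise, the t-test's type I error is roughly 6 to 7%. It is 5.5–5.8% if N is re-set only when the difference favours RFID, and there is no inflation under a rule limited to conditional power of 30–80%.

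These figures assume normal scores, an interim at half of the plan, the rules and caps listed, and no effect of the propensity matching, which was not simulated. They describe the t-test alone, not the two-step decision. Inflation is possible under the text; it has not been shown to have occurred. The matter deserves correction because an accurate rationale costs almost nothing.

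**What to change.** Replace the rationale under Sample size calculation with wording such as:

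> The interim re-estimates only the pooled SD of the satisfaction score, without computing group means. The planned target difference is kept fixed. The total may rise, up to a stated cap, but not fall below 80. For this reason alpha is not adjusted.

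Before this is written, reconcile the target difference in points: 1.125 (11% of the scale), about 23% and about 20% cannot all describe the same difference on a 0–10 score. No figure should be inserted until that is done.

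As 64 patients are already recruited, record what the interim computed and whether N was changed. If the observed group difference was used to change N, analyse the final data with a combination test, for example inverse-normal, with weights fixed by the originally planned 50/50 split. Patients before and after the interim would then be analysed as separate stages, with the matching done within each.

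The wording change itself costs no patients. Its price is that the re-estimation cannot react to an effect smaller or larger than planned. An SD taken over all scores also absorbs part of any true difference. At 1.125 points, used only for illustration, the variance would be 1.5² + 1.125²/4 = 2.25 + 0.32 = 2.57, about 14% above 2.25, so N would err slightly high.
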